#### TIPS for training module

The TIPS module applies MI principles and strategies to address attitudinal barriers through elicitation of change talk and improve engagement in training [100]. AIM HI and CPRT trainers (in the TIPS conditions only) will incorporate MI during training and ongoing consultation/coaching with providers using established MI approaches to increase provider engagement and problem solving throughout the training process [101]: 1. *Pre-training call*: Prior to AIM HI or CPRT initial didactic workshops, providers will receive a pre-training call designed to provide information about training and the intervention, and promote change talk around training (What do you anticipate to go well during this training? Why is this training important to you?). 2. *Proactive planning*: During the initial workshop, trainers will elicit change talk about participating in the EBI training. (e.g., “What would you like to accomplish during this training?” “What do you see as the benefits of getting started in this intervention?”). Trainers will have discussions that elicit self-motivational statements about provider plans for using the intervention strategies, attending training, and adhering to the training plan (e.g., “What steps can you to take to include strategy X in this week’s session?”). Trainees will emphasize autonomy and build confidence in the use strategies and problem solving any challenges. Planning worksheets will include affirmations of strengths and change efforts during each session. 3. *On-going reflection*: During each coaching/consultation session, providers will reflect on the importance of the training and their confidence in their use of the strategies at the beginning and end of each session. Trainer feedback will be tailored to link provider behavior to changes in child or parent behavior. Trainers will use reflective methods to facilitate provider independence with the strategies, relate training to broader professional development, and develop possible solutions and next steps for any challenges—sessions will end with collaborative development of next steps. 4. *Motivational notes*: Providers will receive a weekly motivational text or email (depending on preference) to encourage on-going participation. Messages will be based on identified attitudinal barriers for each participant. They might include motivational texts and/or reminders about attendance and practice and therapy outcomes.

TIPS fidelity will be assessed using the 12-item MI Coach Rating Scale (MI-CRS) [102] developed by [name], the MI expert on the study. Trainers will provide audio recordings of their interactions with providers three times monthly following training and then quarterly thereafter. A similar sample of training sessions for trainers using only standard training (not trained in MI) will be coded to ensure they are not using MI strategies. TIPS fidelity will be examined across sites during ongoing supervision, and concerns will be readily addressed.

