### Provider training procedures

The training curricula follow the manual in both cases. Consistent with our previous studies, training and coaching will be conducted by MA or postdoctoral level researchers with extensive training and experience with AIM HI or CPRT. (Refer to Table 2 for a summary of the training components and process.) AIM HI and CPRT have established training plans developed based on the current knowledge of adult learning theory, health care provider behavior change [90, 91], and data from our pilot and effectiveness studies. Although there is variability in scheduling and details based on the needs of the specific provider group (i.e., therapists or teachers), training in both interventions includes active, systematic, direct, and explicit instructional methods (e.g., step-wise training of general principles then specific strategies; interactive, structured performance-based feedback on skill-building; practice with feedback; sustained training efforts) that have been associated with improved provider competence and patient outcomes [90–95]. The inclusion of ongoing coaching/consultation in both models is especially important for improving and maintaining treatment integrity and provider confidence in their ability to use the intervention [96, 97].

**Table 2 Tab2:** ASD EBI provider training components

	AIM HI	CPRT
Initial didactic training—lecture material, video examples, case illustrations, and hands-on practice with coaching and discussion	12 h (over 2 days)	8 h
Ongoing consultation/coaching—occurs while provider delivers intervention to target child and includes video-based feedback^1^	11 1-h sessions over 6 months (9 group, 2 indiv.)	4 1-h group sessions and 6 individual coaching sessions over 5 months
Total length of training	22 h/6 months	18 h/6 months

^1^Trainers will review videos submitted by providers at least monthly to provide performance feedback during consultation/coaching sessions

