## Data analysis

### General data analytic plan for aims 1–3

All data analytic strategies will follow the recommendations of Brown et al. and the Prevention Science and Methodology Group for randomized field trials [103]. Preliminary data screening and cleaning will require examination of the data distributions for normality and missing data patterns at both the univariate and multivariate level. Preliminary data analysis will also be conducted to determine if there are significant differences between the two studies (CPRT and AIM HI) on target variables. If no significant differences are found, data from the two studies will be integrated to maximize the available data for specific analyses. In the case that outcome variables differ by study, variables representing study will be included as a covariate in all models. Some of the target outcome variables in the two studies were measured using different scales (e.g., AIM HI and CPRT Fidelity). To ensure comparability on these measures, variables will be converted to *z*-scores before statistical comparisons are made. Hierarchical linear modeling (HLM) will be used as the primary, but not only, statistical model due to the nested structure of the data and when the outcome measure is at the provider/outcome level: repeated measures [level-1] nested within providers/children [level-2] nested within program/district [level-3]). Possible clustering effects will initially be estimated by examining intraclass correlation coefficients to determine if accounting for clustering is necessary. All analyses will use an intent-to-treat approach for the TEAMS groups. Because the TEAMS condition variable will contain four groups, three dummy-coded variables will be created and used as predictor variables in target statistical models. To account for the different type of leader at the program/district level, a level-3 binary variable representing whether or not the agency/district leader is a director or a first-level leader will be used in all analyses. Covariates (e.g., baseline scores) may be included in the models to adjust for nonequivalence at baseline and to minimize bias. All analyses will use AR(1) to model a first-order autoregressive correlation structure for the repeated-measures data. Missing data common to longitudinal designs is readily incorporated in HLM if the data can be assumed to be missing at random. However, because there is no statistical test of data that is missing at random [104], all data analysis will also employ selection models [105] to model relationships of interest for the data missing not at random mechanism, as recommended by Little and Rubin [106]. Of interest in some of proffered hypotheses are the differences in target outcomes between the TEAMS groups over time. The TEAMS groups will be statistically compared when a significant cross-level (Time X TEAMS Group) interaction is evident using the statistical methods of Preacher, Curran, and Bauer [107].

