
#### Specific analyses for aim 1: test the effectiveness of the TEAMS modules individually and in combination on implementation outcomes when paired with two ASD EBI

To determine if there are significant main effects and interactions between the TEAMS groups on observed therapist fidelity (based on video recorded sessions coded at 3 time points over 6 months), statistical analyses will proceed using the 3-level nested data structure outlined in the General Analytic Plan section. To determine if there are significant differences between the TEAMS groups on observed child behaviors during sessions, statistical analyses will proceed using the 3-level nested data structure outlined in the General Analytic Plan section. To determine if there are differences between the TEAMS groups on child symptoms (EBCI or PDDBI) at 6 months, the 3-level nested data structured will be used.

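### Trainers are nested within TIPS status, but the three-level model and the variance inflation factor allow only for program/district clustering, so contrasts across TIPS status are tested too liberally if trainers serve several programs

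*Protocol article*

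**What the plan says.** Under TIPS for training module, the article says "AIM HI and CPRT trainers (in the TIPS conditions only) will incorporate MI during training and ongoing consultation/coaching with providers". For the fidelity check on the comparison conditions, it says "A similar sample of training sessions for trainers using only standard training (not trained in MI) will be coded". A trainer who has been trained in MI cannot also belong to that second group, so the two sets of trainers do not overlap.

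Under Provider training procedures, "training and coaching will be conducted by MA or postdoctoral level researchers with extensive training and experience with AIM HI or CPRT". The number of trainers, the number of programs that each one covers, and how they are assigned to MI or standard delivery are not given. The Randomization section covers programs and districts only.

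The General data analytic plan sets the data structure as "repeated measures [level-1] nested within providers/children [level-2] nested within program/district [level-3"). For fidelity, the primary outcome, the aim 1 section says "statistical analyses will proceed using the 3-level nested data structure outlined in the General Analytic Plan section", and it uses the same structure for child session behavior and child symptoms. Aim 2 uses it for provider attitudes. The predictors and covariates named are three condition dummies, study, leader type and baseline scores. The Power analyses section inflates for program/district clustering only (VIF = 1.28, from 8 providers per program and ICC = 0.04). No model, covariate list or inflation factor includes trainer.

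**The concern.** TIPS is delivered through the trainer. Trainers run the initial workshop, give video-based feedback and coach each provider for five to six months (Table 2). They also supply the attendance ratings behind training completion and part of provider engagement (Table 3). Some trainers will be better than others, and that variation can reach fidelity and completion whether or not MI is used.

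A program random effect absorbs a trainer's influence within a program, but it treats two programs coached by the same trainer as independent. Because no trainer appears on both sides of the TIPS factor, trainer variation does not cancel in a TIPS contrast. It stays in the estimate but is understated in the standard error. The trial's purpose is to separate the effects of its two modules, so the validity of the TIPS test matters.

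**Working it through.** **The plan's own figure.** Inputs from Power analyses: two-sided alpha 0.05 (sidedness assumed), power 0.80, d = 0.39, attrition 30%, AR(1) correlation 0.60, VIF 1.28. Three fidelity time points come from the aim 1 section.

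- VIF = 1 + (8 − 1) × 0.04 = 1.28.
- Variance of the generalized least squares average of three AR(1) measures at 0.60: v = 0.667.
- n per group before inflation = 2 × (1.960 + 0.842)² × 0.667 / 0.39² = 68.8.
- With clustering and attrition: 68.8 × 1.28 / 0.70 = 125.8 per group; × 4 groups = 503.3.

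The article states 502 in 63 programs/districts (502/8 = 62.75). The figure reproduces closely with no trainer component, so the plan's variance covers program clustering alone.

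**Adding trainers.** Assume one trainer per program, each trainer covering several programs on one side of the TIPS factor. Let n be providers per side, k programs per side, T trainers per side, ICCp = 0.04 (stated) and ICCt the trainer ICC (assumed, added to ICCp).

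- True variance of a side mean = (1 − ICCp − ICCt)/n + ICCp/k + ICCt/T
- Variance the three-level model sees = (1 − ICCp − ICCt)/n + (ICCp + ICCt)/k
- Type I error = 2 × [1 − Φ(1.96 / √ratio)], where ratio = true/model variance

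Pooled TIPS against no TIPS: n = 590/2 = 295, k = 74/2 = 37. Pairwise arm contrast: n = 590/4 = 147.5, k = 74/4 = 18.5.

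Worked case, pooled, T = 4, ICCt = 0.02:

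- True variance: 0.94/295 + 0.04/37 + 0.02/4 = 0.00319 + 0.00108 + 0.00500 = 0.00927.
- Model variance: 0.94/295 + 0.06/37 = 0.00319 + 0.00162 = 0.00481.
- Ratio 1.93, so the true standard error is 1.39 times the model's, and type I error is 15.8%.

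| Trainers per side (pooled) or per arm (pairwise) | Pooled, ICCt 0.01 | Pooled, ICCt 0.02 | Pairwise, ICCt 0.01 | Pairwise, ICCt 0.02 |
|---|---|---|---|---|
| 4 | 10.8% | 15.8% | 7.5% | 9.9% |
| 6 | 8.6% | 11.9% | 6.4% | 7.8% |
| 10 | 6.9% | 8.6% | 5.6% | 6.1% |
| One per program | 5.0% | 5.0% | 5.0% | 5.0% |

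**Checks.** Taking the trainer share out of the stated 0.04 instead of adding it, and allowing for shared trainers also shrinking the observed between-program variance, gives nearly the same pooled results: 11% and 17% with 4 trainers per side (ICCt 0.01 and 0.02), 7% and 9% with 9. A simulation with 4 trainers per side and ICCt 0.02 gave 16 to 17%.

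**Power.** For a pairwise contrast at 590 providers, power is 0.86 with program clustering only. With the trainer share taken out of 0.04 at ICCt 0.02, it is 0.71 with 4 trainers per arm and 0.81 with 9.

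**The case against.** The strongest objection is that the key premise is not in the article. Inflation needs trainers to serve several programs, and the number of trainers, their spread over programs and their ICC are all unstated. This stands as a limit on certainty. Against it, avoiding the problem would take about 37 different trainers on each side, all experienced in one of the two interventions.

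Second, the pooled test may not be the one used. The plan codes four groups with three dummies, compares groups after a significant Time × Group interaction, and powers for a difference between at least two groups. The aim 1 section does mention main effects, so the pooled test cannot be excluded, but the pairwise figures deserve equal weight. The formula also treats a single mean, not the change from a PRE measure taken before EBI training.

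Third, a reader might infer much larger errors. A trainer ICC of 0.05 gives 25.9% for the pooled test with 4 trainers per side, but adding 0.05 to the stated 0.04 implies program-level clustering of 0.09, more than twice the article's figure. Nothing in the article supports that. Four trainers per side also means two per intervention, covering three counties and three waves, so that row is the extreme end of the range.

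Fourth, this is a condensed article that calls HLM the primary but not the only model and monitors trainer fidelity. Trainer numbers may well be in the full protocol. But the article does state its levels and its sources of clustering, and these omit the level at which TIPS is delivered, so the point is not merely a detail left out.

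**Conclusion.** The concern holds in conditional form. Trainers are nested within TIPS status by the article's own description, and neither the model nor the inflation factor accounts for them. If trainers serve more than one program, the standard error for contrasts across TIPS status is too small. Type I error is then about 7 to 16% (pooled) or 6 to 10% (pairwise) at nominal 5%, assuming 4 to 10 trainers per side or arm and a trainer ICC of 0.01 to 0.02. With one trainer per program there is no inflation. Comparisons of TLI within the same TIPS status (TLI against STANDARD, TLI + TIPS against TIPS) are not confounded in this way, since trainers can be shared across them.

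Two stronger readings are not supported. One is that the standard error is certainly too small: that depends on an allocation the article does not describe. The other is that the effective sample for TIPS is close to the number of trainers. Over the assumed range, the pooled variance ratio is 1.16 to 1.93, equivalent to 37/1.16 = 32 down to 37/1.93 = 19 independent programs per side, still well above 4 to 10.

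**What to change.** - Record trainer ID for each provider.
- Add a trainer random effect, nested in TIPS status and study, with small-sample degrees of freedom, to the provider- and child-level models: fidelity, training completion, child outcomes, provider attitudes and engagement. Trainer cannot be a fixed effect because it is aliased with TIPS. The leader-level leadership and climate models do not need the term.
- Report the number of trainers and the trainer variance per arm.
- State how trainers were allocated to MI or standard delivery. Unless this was random, state as a limitation that the random effect corrects the standard error but does not remove systematic differences between the two trainer sets.

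The cost is one identifier per provider and one model term. The downside is a wider interval for TIPS, and an unstable variance estimate if trainers are few.

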### Procedures for randomization and data collection

#### Randomization

Programs and districts will be randomized by an independent researcher and stratified by county and study via computer-generated randomization to one of four conditions per study following official study enrollment

#### TLI

For the 2 groups randomized to TLI or TLI + PROV, the initial TLI workshop will be completed before provider enrollment. This will be done each spring/summer. Each fall, programs, and districts in all conditions will begin provider/child dyad enrollment, complete pre-assessments, and training.

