### Procedures

#### Enrollment procedures

Programs and districts will be recruited in three waves, over 3 years. Once programs are enrolled, leaders from within the enrolled programs/districts will be recruited. Potentially eligible providers will then be recruited through presentations at standing staff meetings or team meetings. Providers will then identity potentially eligible family participants from their caseload or classrooms and will obtain permission for the research team to contact the caregiver to recruit for participation. All participants will be provided information about the study from research staff and provide consent obtained prior to data collection.

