#### Outcome measures

Because we are testing an implementation intervention and our ASD EBI have been shown to be effective in our large-scale effectiveness trials, our primary measures are related to provider implementation (training completion/fidelity). However, consistent with Hybrid, type 3 designs, we will collect child outcome data as secondary outcome measures (within session behavior; standardized measures). Outcomes will be collected for leaders and providers using the following timeframes: Baseline (BL—initial program/district enrollment), Pre (PRE—prior to EBI Training), Post training (POST—6 months after initiation EBI training), and Follow-Up (12 months post PRE). Parents will complete child measures at PRE and POST as children may not remain with the same provider or be receiving services at follow-up. Data will be collected by administering a brief battery of measures (including demographic measures for all participants) via on-line survey or phone interview. The outcome constructs include implementation outcomes (provider and child) as well as measurement of the specific mechanisms of change expected from the implementation intervention. Refer to Table 3 for specific outcome measures and timing.

**Table 3 Tab3:** Study measures

Purpose (aim)	Construct	Measure/indicators	Timeframe			
			BL	Pre	Post	FU
Outcomes (aim 1)	Training completion	Provider training/consultation completion (based on trainer-rated attendance tracking)			X	
	Provider fidelity	Fidelity of ASD EBI (*also collected mid-training for total of 3 obs.*)		X	X	.
	Child improvements	Child session behaviors (disruptive, engagement)		X	X	
		Child symptom improvement (ECBI [AIM HI]/PDDBI [CPRT])		X	X	
Mechanisms of change (aims 2, 3)	Provider engagement	Training/consultation attendance (trainer rated)			X	
		Adherence to training requirements (video submissions, forms)			X	
	Provider attitudes	Evidence-Based Practice Attitudes Scale (EBPAS)		X	X	X
		Adapted motivation inventory [116]		X	X	X
	Impl. Leadership & Climate	Implementation Leadership Scale (leaders and providers) [98]	X	X	X	X
		Implementation Climate Scale [117] (leaders and providers)	X	X	X	X
	Implementation support use	Assessment of implementation supports strategies	X	X	X	X
Moderators (aim 3)	Background/experience	AIM HI & CPRT Background Questionnaire (leaders & providers)	X (L)	X (P)		
	Org. structure	Program/District Structure Questionnaire	X			

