#### Specific analyses for aim 2: test the impact of TEAMS modules on leader- and provider-level mechanisms of change

Measurement of leader-level outcomes is of primary interest. Implementation Leadership and Climate scores will be aggregated to the leader level. For this reason, HLM models (or single-level regression models if ICC values suggest clustering is negligible) will be used to test for TEAMS group differences on measures of implementation leadership and climate scores at 6 and 12 months. These analyses will control for baseline scores on these measures. To determine if there are significant differences between the TEAMS groups on therapist attitudes (EBPAS), analyses will proceed using the 3-level nested data structure outlined in the General Analytic Plan. These analyses will control for baseline EBPAS scores.

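### For measures first taken at PRE, the baseline follows randomisation and the TLI workshop, so adjusting for it or measuring change from it removes any TLI effect already present

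*Protocol article*

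**What the plan says.** Programs and districts are allocated to "one of four conditions per study following official study enrollment" (Randomization). In the arms that include TLI, "the initial TLI workshop will be completed before provider enrollment. This will be done each spring/summer" (TLI). Then: "Each fall, programs, and districts in all conditions will begin provider/child dyad enrollment, complete pre-assessments, and training".

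The time points are defined as "Baseline (BL—initial program/district enrollment), Pre (PRE—prior to EBI Training" (Outcome measures). Table 3 schedules leadership, climate and implementation support use at BL, PRE, POST and follow-up, with leaders and providers named as raters of leadership and climate. EBPAS and the motivation inventory start at PRE. So do fidelity and the child measures.

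For leadership and climate, the aim 2 analysis states: "These analyses will control for baseline scores on these measures". For attitudes: "These analyses will control for baseline EBPAS scores". For aim 1, the general analytic plan makes baseline covariates optional, and compares groups over time when the Time x Group interaction is significant.

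Providers come in after their leaders: "Potentially eligible providers will then be recruited through presentations at standing staff meetings or team meetings" (Enrollment procedures). The same section requires consent before data collection.

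**The concern.** A baseline covariate is safe in a randomised comparison because allocation cannot have influenced it. PRE lacks that protection for TLI. It is taken after allocation, and in two of the four arms after leaders have been trained and have drawn up a plan for supporting the intervention. If that has already moved a provider's attitudes or practice, conditioning on PRE, or measuring change from it, takes the early part of the effect out of the estimate and biases it toward zero.

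This bears on a main hypothesis. Aim 1 compares the full model with standard training and with each single module. Two of those three comparisons (full v standard, full v TIPS) differ in TLI exposure.

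A related exposure is that providers volunteer, and identify the child, after their leader's workshop. The background section on provider attitudes links pre-training attitudes to later fidelity, so uneven volunteering between arms could also matter, in a direction that cannot be foreseen.

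**Working it through.** **1. Order of events.** Program enrolment and BL; randomisation; TLI workshop (spring/summer, TLI arms only); provider and child enrolment and PRE (fall); EBI training; POST. PRE is therefore post-randomisation in every arm and post-workshop in the TLI arms.

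**2. Which baseline each measure has.**

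| Measure | First score | Use of baseline |
|---|---|---|
| Leadership, climate | BL | Adjustment required; time point not named in aim 2 |
| Support use | BL | Not specified in aim 2 |
| EBPAS | PRE | Adjustment required; can only be PRE |
| Motivation inventory | PRE | Not specified |
| Fidelity, child outcomes | PRE | Covariate optional; Time x Group starts at PRE |
| Training completion | POST | None needed |

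**3. Who can rate at BL.** Table 3 has providers rating leadership and climate at BL, and the TLI module section has them rating in the assessment listed before the initial TLI training. But Enrollment procedures recruits providers after leaders, and the TLI paragraph enrols them after the workshop. Table 3 itself places the background questionnaire at BL for leaders and at PRE for providers. These places do not agree.

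**4. The plan's own sample size.** Inputs from Power analyses: alpha 0.05, power 0.80, d = 0.39, autocorrelation 0.60, attrition 30%, VIF = 1 + 7 × 0.04 = 1.28. The variance of the generalised least squares mean of three AR(1) measures is (1 + 0.6)/(3 − 0.6) = 0.667.

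- n per group = 2 × (1.96 + 0.842)² × 0.667 / 0.39² = 68.8
- 68.8 / 0.7 = 98.3; × 1.28 = 125.8; × 4 groups = 503, against the stated 502.

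The matching formula averages a constant group difference over all three time points, PRE included. It does not power a change from PRE.

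**5. What is removed.** Let d be the true TLI effect at POST, f the share of it already present at PRE, and b the PRE–POST slope.

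- Change or Time x Group contrast: d(1 − f)
- POST adjusted for PRE: d(1 − b·f)
- POST unadjusted: d

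The article gives no f, so a range is shown. I take b = 0.36 (0.60², PRE to POST with a mid-training observation between) to 0.60 (adjacent observations, as for EBPAS), borrowing the plan's autocorrelation. d = 0.39 serves as a scale only; the plan took it from the effect of training on teacher fidelity, not of TLI.

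| f | PRE-adjusted, b = 0.36 | PRE-adjusted, b = 0.60 | Change |
|---|---|---|---|
| 0 | 0.390 | 0.390 | 0.390 |
| 0.10 | 0.376 | 0.367 | 0.351 |
| 0.25 | 0.355 | 0.332 | 0.292 |
| 0.50 | 0.320 | 0.273 | 0.195 |
| 1 | 0.250 | 0.156 | 0 |

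A simulation of 74 clusters of 8 with ICC 0.04 (1,500 runs per setting) agrees. At f = 0.50 the adjusted estimates were 0.316 and 0.268, and the change estimates 0.196 and 0.193.

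**6. Power, TLI v no TLI.** Effective n per side = 295 × 0.7 / 1.28 = 161.3. For the change contrast (SD √(2 × 0.64) = 1.13), power is 0.87 at f = 0, 0.80 at 0.10, 0.64 at 0.25 and 0.34 at 0.50. For the PRE-adjusted contrast it is 0.96 to 0.99 at f = 0 and about 0.87 at f = 0.50. For unadjusted POST, SE = √(2/161.3) = 0.111 and 0.39/0.111 = 3.50, so power is about 0.94 whatever f is.

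**7. Cost of not adjusting.** The SE ratio is 1/√(1 − ρ²): 1.07 at ρ = 0.36 and 1.25 at ρ = 0.60. Setting (1 − ρf)/√(1 − ρ²) = 1 gives f = 0.19 and 0.33. Below those shares PRE adjustment keeps more power, although it is biased whenever f > 0.

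**The case against.** The case against is substantial and narrows the point.

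- **TLI's direct targets have a pre-workshop score.** The article itself labels BL as baseline, so the natural reading of the leadership and climate adjustment is BL, and nothing is then lost. These scores are aggregated to leader level, so the same individuals need not supply them at every time point. This stands, provided BL ratings can actually be collected.
- **Attitudes are assigned to TIPS.** Aim 2 expects TIPS, not TLI, to change attitudes. TIPS v standard, and TIPS + TLI v TLI, compare arms with the same workshop exposure. This stands: workshop timing does not bias those contrasts.
- **Aim 1 is less exposed than it looks.** Covariates are optional, training completion is measured only at POST, and the aim 1 text tests main effects as well as interactions. This stands too; what remains is the Time x Group contrast on fidelity and child outcomes.
- **Little may have moved by PRE.** The initial TLI session lasts three hours, the article does not date the start of leader coaching, and providers have not yet been trained in the EBI. For fidelity this is persuasive. For attitudes it is less so.
- **Dropping PRE has its own risk.** If TLI arms attract keener volunteers, PRE adjustment corrects part of that imbalance and an unadjusted POST contrast none of it. This is right, and argues for reporting both.

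A reader might also infer that PRE is contaminated by TIPS, because before the workshops "providers will receive a pre-training call designed to provide information about training and the intervention, and promote change talk". The article does not order that call against PRE. That is silence on an operational detail which an article may leave to the full protocol, not a stated error.

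**Conclusion.** The point holds in a limited form. For EBPAS, motivation, fidelity and child outcomes, PRE is not a pre-intervention baseline where arms differ in TLI. The required EBPAS adjustment and the Time x Group test on fidelity and child outcomes remove whatever TLI effect is present by then: a share f of it for change contrasts, and b·f for adjusted ones. The contradiction over who supplies provider ratings at BL is separate and is on the page.

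Two stronger readings are tempting and are not supported. One is that part of the TLI effect certainly is removed, or that a stated percentage is. The documents give no shift at PRE, and the figures above rest on an assumed f (from zero upward), the plan's autocorrelation borrowed for b, and 0.39 as a scale. The other is that every provider-rated baseline is post-intervention. Table 3 schedules leadership and climate at BL, and support use has a BL score as well.

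**What to change.** 1. In the aim 2 analysis, name BL as the covariate for leadership and climate. Collect it in all four arms from leaders and current staff before allocation is disclosed, and aggregate it to leader level. Reconcile Table 3 and the TLI module section with Enrollment procedures and the TLI paragraph on when providers can give ratings.
2. For PRE-only measures, do not treat PRE as a pre-intervention baseline in contrasts that differ in TLI. Report the POST contrast both without and with PRE adjustment, and test the PRE difference by TLI arm. Keep PRE adjustment for TIPS contrasts within the same TLI level.
3. Have each program or district list its eligible providers at BL, before allocation is disclosed, and report enrolment by arm against that list.

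The cost is a short amendment and one staff list per program or district; the BL survey is already scheduled. The unadjusted TLI contrast has standard errors about 7% (ρ = 0.36) to 25% (ρ = 0.60) wider and does not correct for differential volunteering, so it should stand beside the adjusted version rather than replace it.
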